**Figure 6 fig6:**
[figure not shown]
Medical infrared thermography image. The black rectangle delineates the area where data collection occurs.

### Sample size calculation

Derived from preliminary trial results, this study divides patients into two groups via a randomized approach. The primary efficacy endpoint is assessed using the Visual Analog Scale (VAS) scores within the Short-Form McGill Pain Questionnaire (SF-MPQ), with observed mean VAS scores of 2.40 and 3.60, alongside standard deviations of 1.10 and 1.50, for the two groups, respectively. Utilizing G*Power 3.1.9.2 for statistical calculations, with a test significance level (α) set at 0.05 and a power (1-β) of 0.9 for a two-sided test, the sample size requirement for eachup is determined to be 27 participants (32). Factoring in a 10% potential dropout rate, this necessitates 30 participants per group for both the observation and control cohorts.

$$N=2\times {\left[\left(Z_{\alpha /2}+Z_{\beta /2}\right)\times \sigma /\delta \right]}^{2}$$

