### Observational indicators

#### Primary observational indicators

##### Short-Form McGill Pain Questionnaire (SF-MPQ)

Pain evaluation is performed using the SF-MPQ, a globally recognized instrument for describing and quantifying pain experiences (29). The SF-MPQ consists of three main components: the Pain Rating Index, which assesses the quality of pain; the Visual Analogue Scale for headache, offering a subjective measure of pain intensity; and the Present Pain Intensity section, which provides a snapshot of the current pain level.

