### Data analysis

The principle of Intention-To-Treat (ITT) analysis and Per-Protocol (PP) analysis will be followed in the process of statistical analysis. Descriptive analysis will be used for the baseline characteristics of the patients in each group, data will be presented as mean or median with standard deviation or interquartile range for continuous variables and as frequency distributions for categorical variables. Two-sample t-test for quantitative data or Chi-square test for qualitative data will be performed as homogeneity test, and analysis of covariance will also be performed if an adjustment is needed for a baseline characteristic. For quantitative data that do not conform to a normal distribution, data are expressed as median (IQR). In all analyses, statistical significance will be accepted as a 2-tailed *p* < 0.05. For the primary outcome, SF-MPQ scores will be assessed by using the linear mixed-effects model with the interaction effects of time and group. Participants who do not complete the study will be treated as having no change from baseline at all times. A Bonferroni correction will be used to account for multiple comparisons. Correlation analysis will be conducted between the difference of medical infrared thermography (MIT) and the other outcome measures by the Pearson correlation analysis. All statistical analyses will be conducted with SPSS software, version 25.0 (SPSS Inc).

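### The stated 90% power belongs to one uncorrected VAS comparison, whereas the plan makes the whole SF-MPQ primary, tested by a time-by-group interaction with a Bonferroni correction of unstated scope

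*Protocol article*

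**What the plan says.** **Endpoint.** Under Sample size calculation the protocol article states "The primary efficacy endpoint is assessed using the Visual Analog Scale (VAS) scores within the Short-Form McGill Pain Questionnaire (SF-MPQ"). No visit is attached to it. The abstract and the section on primary observational indicators make the SF-MPQ itself primary. The latter says "The SF-MPQ consists of three main components" (Pain Rating Index, VAS, Present Pain Intensity) and does not choose among them.

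**Visits.** The abstract and Trial design give five assessments: baseline and four later ones (days 3, 15, 30 and 60 in the abstract).

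**Analysis.** Under Data analysis, for the primary outcome, "SF-MPQ scores will be assessed by using the linear mixed-effects model with the interaction effects of time and group". The same section says "In all analyses, statistical significance will be accepted as a 2-tailed" p below 0.05, and also "A Bonferroni correction will be used to account for multiple comparisons". It does not say which comparisons the correction covers.

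**Sample size inputs.** "observed mean VAS scores of 2.40 and 3.60" and "standard deviations of 1.10 and 1.50, for the two groups, respectively", two-sided alpha 0.05, power 0.90, computed in G*Power. The result is 27 per group, raised to 30 for 10% dropout. The formula printed beneath adds the normal quantiles for alpha/2 and for beta/2.

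**The concern.** The sections give two different primary endpoints: one score, or a questionnaire with three scores. They also give two different primary tests: a difference between two means, or an interaction over repeated visits with a multiplicity correction. The sample size matches the first of each pair and the analysis section matches the second. A separate analysis plan could fill in detail, but it could not settle this without overriding one of the protocol's own statements.

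At stake is what counts as a positive trial. With three scores and four follow-up visits there are up to 3 x 4 = 12 between-group comparisons, and the text does not say which of them decides. If the correction applies to the deciding comparisons, the stated power was calculated at a more lenient alpha than the one that will be used. The printed formula is a further, smaller inconsistency, because it does not give the 27 stated beside it.

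**Working it through.** **Inputs (all from Sample size calculation).** Difference 3.60 - 2.40 = 1.20; SDs 1.10 and 1.50; two-sided alpha 0.05; power 0.90; 27 per group, 30 after dropout.

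**1. Reproducing the plan's figure.**
- Pooled SD = sqrt((1.10² + 1.50²)/2) = 1.315.
- Standardised difference d = 1.20/1.315 = 0.912.
- Two-sample t-test, noncentral t with 2n - 2 degrees of freedom and noncentrality d x sqrt(n/2). At n = 27 the noncentrality is 0.912 x sqrt(13.5) = 3.35 and power is 90.8%. This is the smallest n that reaches 90%.
- Dropout: 27/0.9 = 30.

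So 27 and 30 are correct for one VAS comparison at an uncorrected 0.05.

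**2. The printed formula.** N = 2 x [(sum of the two quantiles) x SD/difference]².
- As printed, with the beta/2 quantile (1.645): 2 x [(1.960 + 1.645) x 1.315/1.20]² = 31.2, so 32 per group.
- With the beta quantile (1.282): 2 x [(1.960 + 1.282) x 1.315/1.20]² = 25.2, so 26. The t-test gives 27.

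The stated 27 agrees with the t-test and not with the formula as printed.

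**3. Effect of a Bonferroni correction on one pre-named comparison.** Same noncentral t, alpha = 0.05/m. Assumption: every score and visit has the VAS effect d = 0.912. The document gives figures for the VAS only.

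| Family (m) | Power, 27 per arm | Power, 30 per arm | n per arm for 90% | After 10% dropout |
|---|---|---|---|---|
| One VAS test (1) | 90.8% | 93.5% | 27 | 30 |
| Three scores (3) | 80.7% | 85.4% | 34 | 38 |
| Four visits, VAS only (4) | 77.4% | 82.6% | 36 | 40 |
| Three scores x four visits (12) | 63.9% | 70.6% | 44 | 49 |

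The 30-per-arm column matters because the plan names an intention-to-treat analysis with non-completers carried as unchanged from baseline.

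**4. How far other assumptions move these figures (m = 3, 4, 12).**
- 30 per arm, effect diluted by 10% for non-completers set to no change: 76%, 73%, 58%.
- 27 per arm, baseline adjustment with an assumed correlation of 0.5: 92%, 90%, 80%.
- 27 per arm, chance that at least one comparison passes the corrected alpha, by simulation: 95%, 96%, 97% at an assumed correlation of 0.5 between comparisons; about 92% to 93% at 0.7; 88%, 87%, 82% at 0.9.

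**The case against.** The strongest reply is that no loss of power has been established. The analysis section does not set the Bonferroni family at 3, 4 or 12. The correction might apply only to visit contrasts after a single interaction test, and the sample size section does name the VAS as primary. On that reading 90.8% stands. If any one corrected result would count as success, step 4 shows that the chance of at least one stays near or above 90% unless the comparisons are highly correlated. Model detail is also commonly left to a fuller document. All of this stands against a flat statement that power is 64% to 81%. It does not remove the contradiction over which outcome and test are primary.

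Four stronger readings are tempting, and the document does not support them:

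- **That family-wise error reaches 46%.** 1 - 0.95^12 = 0.46 describes twelve independent tests with no correction. The plan commits to one, and adjusted p-values are routinely compared with 0.05, so the two statements about significance need not conflict.
- **That the trial is short by 12 patients.** The printed formula would give 32/0.9, so 36 per group and 72 in total against 60. But the 27 came from the t-test, where it is right. The formula is a misprint that did not drive the size.
- **That the interaction test would miss a constant benefit.** This is true only if baseline is a covariate and not one of the modelled times. The document does not say so, and it lists baseline among the five assessments. On that reading a constant post-baseline benefit does produce an interaction.
- **That day 3 should be ruled out as the primary visit.** The document does not say at which visit the preliminary means were observed, so there is no ground for excluding any.

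**Conclusion.** The point holds as an inconsistency with a conditional cost. The 90% power applies to one uncorrected two-sample VAS comparison at an unnamed visit. The analysis section plans a time-by-group interaction on SF-MPQ scores with a Bonferroni correction that the sample size ignores.

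If the correction reaches the primary comparisons, power for a given pre-named comparison falls to about 81%, 77% or 64% with 27 per arm, or 85%, 83% or 71% with 30, for families of 3, 4 or 12. These figures rest on the VAS effect holding for every score and visit, on a t-test rather than the mixed model, and on family sizes that the document does not state. Baseline adjustment could raise them and imputing no change could lower them.

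The printed formula is wrong; the stated 27 and 30 per group are not.

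**What to change.** - Reconcile the abstract, the outcome section, the sample size section and the data analysis section on one primary endpoint: SF-MPQ VAS at one pre-specified follow-up visit, the one to which the preliminary means of 2.40 and 3.60 refer. The sponsor needs to state which visit that is.
- Test it at two-sided 0.05 as the between-group contrast at that visit from the mixed model.
- Make the Pain Rating Index, the Present Pain Intensity and the other visits secondary, and confine Bonferroni or Holm to them.
- If several scores or visits are to stay primary, state the Bonferroni family and restate the power, or the sample size, for it.
- In the printed formula, replace the beta/2 quantile by the beta quantile.

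The cost is wording in these sections. The Pain Rating Index and the Present Pain Intensity lose primary status. With a single primary comparison no extra patients are needed, and the 27 and 30 per group then apply to the test that decides the trial.

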### Randomization and blinding

The study employs a simple randomization technique, utilizing SPSS 20.0 software for sequence generation, random seeding, and group allocation. Produced and stored in sealed opaque envelopes, randomization cards facilitate assignment anonymity. Eligibility confirmation leads to an envelope opening by researchers external to the treatment, assessment, and statistical analysis processes, ensuring that participant assignment is devoid of bias. Blinding extends to statisticians and data handlers, who remain uninformed of group allocations until post-treatment, enhancing study integrity. Participant treatment is conducted in separate rooms to prevent inter-subject communication.

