**Methods and analysis:**

In this study, we enroll 60 patients experiencing CEH. The control group receives ultrasound-guided injections of GON and TON. The intervention group is treated with ultrasound localization meridian sinew tuina combined with the injection of GON and TON. Meridian sinew tuina is performed once a day for 30 min for 3 days. The primary observational index includes the Short-Form of McGill Pain Questionnaire (SF-MPQ). The Secondary outcomes include Cervical Range of Motion (ROM) and Medical Infrared Thermography (MIT). MIT is used to measure the change in skin temperature in the area of the patient’s meridian sinew tuina treatment of GON and TON before and after the intervention. There are 5 time points assessed as baseline, day 3, day 15, day 30, and day 60.

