### Intervention group: ultrasound localized meridian sinew tuina combined with GON and TON injections

#### Treatment protocol

The intervention entails a regimen of daily meridian sinew tuina therapy for three consecutive days, with each session spanning 30 min, starting from the baseline. On the third day, participants receive a single session of ultrasound-guided injections into the greater and third occipital nerves (GON and TON), marking the completion of the treatment course. Each participant undergoes one full course of this combined treatment.

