##### Medical infrared thermography

*Instrumentation*: The study employs the X640D digital infrared thermography system by Ge Wu You Xin Company. Image analysis is conducted using IRToolPRo software, which provides a comprehensive temperature detection range from 0°C to 300°C with a precision of ±0.3°C. The system boasts a pixel size of 17UM, a frame rate 30 Hz, and operates within the 8 ~ 14UM band. For enhanced visual contrast, the color scale mode is selected.*Testing conditions*: The testing environment is precisely controlled to ensure optimal data accuracy. The laboratory temperature is maintained between 20°C and 23°C, with strict avoidance of any direct sunlight or artificial light exposure and minimal indoor air movement (31). Relative humidity is regulated within the 20 to 30% range, creating ideal conditions for thermographic analysis.*Operational method*: Participants first acclimate to the laboratory environment by resting quietly for five minutes, allowing skin temperature stabilization. They then stand upright, exposing the head and neck area, and position themselves one meter from the infrared thermography camera. The attending physician adjusts the camera focus to ensure the capture of clear thermal images. Infrared thermal data collection encompasses the highest, lowest, and average temperatures at the skin surface areas corresponding to the bilateral greater occipital nerve and the third occipital nerve, as illustrated in Figure 6.

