### Data collection and management

The data collection managers for this study are full-time staff who are clinically trained but not involved in the clinical intervention process, ensuring rigorous verification and accuracy. All findings are strictly derived from original data, with error corrections on case report forms (CRFs) marked without obfuscation. Researchers meticulously document and electronically record patient information, with post-study CRFs securely stored and electronic data fixed against unauthorized modifications. Patient confidentiality is paramount, with participant follow-ups conducted telephonically upon consent.

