This study heralds several innovative approaches and advantages, primarily in clinical treatment met grohodology. Utilizing ultrasound technology, we precisely identify the anatomical locations of the greater and third occipital nerves (GON and TON), enabling targeted meridian sinew tuina. The integration of meridian sinew tuina with GON and TON injections represents a novel approach that may accelerate recovery in cervicogenic headache (CEH) patients, fostering a synergistic effect between sympathetic nervous system and traditional Chinese therapeutic massage (41). The trial’s design is meticulous, ensuring clarity, transparency, and reproducibility, thereby facilitating the possibility of replication by other researchers.

However, this protocol trial is not without its limitations. Being conducted at a single center, the study’s ability to generalize findings across different populations is restricted. Additionally, the intrinsic characteristics of meridian massage preclude the possibility of blinding practitioners and participants, challenging the implementation of a double-blind randomized controlled trial (RCT). Despite these constraints, the study adheres strictly to separation principles among operators, allocators, and statisticians to mitigate potential biases. The rigorous adherence to treatment protocols aims to yield reliable clinical evidence for CEH management.

In conclusion, our randomized controlled clinical trial is meticulously designed to investigate a safe and effective manual therapy protocol, offering a reference point for the clinical management of CEH. Our aspiration is that the findings from this study will furnish theoretical and practical insights, paving the way for future research in this domain.

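### Masking of statisticians and data handlers ends at post-treatment, which as written can precede the later follow-up visits and the analysis decisions

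*Protocol article*

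**What the plan says.** The Randomization and blinding section of the protocol article names who is masked and for how long: "Blinding extends to statisticians and data handlers, who remain uninformed of group allocations until post-treatment".

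The Treatment protocol section fixes when the course ends in the intervention arm: "On the third day, participants receive a single session of ultrasound-guided injections into the greater and third occipital nerves (GON and TON), marking the completion". It adds: "Each participant undergoes one full course of this combined treatment". The control-group section describes the injections but gives no day for them.

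The abstract gives the schedule: "There are 5 time points assessed as baseline, day 3, day 15, day 30, and day 60". The Trial design section gives the same five assessments, but counts the last three from the end of treatment.

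The Data analysis section plans both intention-to-treat and per-protocol analyses, covariance adjustment if a baseline characteristic calls for it, and a different summary for data that are not normally distributed. The primary model, a linear mixed-effects model with a time-by-group interaction, is fixed.

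The Discussion concedes that neither practitioners nor participants can be blinded, and says that "the study adheres strictly to separation principles among operators, allocators, and statisticians" as a way of limiting bias.

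**The concern.** Analysts are masked so that nobody who queries, cleans, classifies or analyses the data can be steered by knowing the arm. That protection has to last until those tasks are finished. Here the stated end point is tied to treatment, which is short, and not to follow-up or database lock, which come later.

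The protocol leans on this safeguard, since it accepts that patients and therapists know the treatment. If masking may lapse once treatment is over, data queries during follow-up, the choice of who belongs in the per-protocol set, the judgement on covariate adjustment and the handling of non-normal outcomes could all be made by people who know the allocation.

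**Working it through.** The plan gives no figure on this point, and the sample size does not enter. The check is a comparison of sections and a count of visits.

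**1. When masking ends.** Randomization and blinding: at post-treatment. The section does not say whether this means each participant's own treatment or the treatment of the whole trial.

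**2. When treatment ends.** Treatment protocol: day 3 in the intervention arm, with one course only, so no further treatment is planned. For controls the day is not stated.

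**3. What post-treatment means elsewhere.** Trial design uses the term, joined to the conclusion of treatment, for the point from which follow-up is counted. Data collection and management uses a different term, post-study, for the time when case report forms are stored. The document's own usage therefore favours post-treatment as the start of follow-up, not the end of the trial.

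**4. Visits after that point.** Post-baseline visits: days 3, 15, 30 and 60, so 4. Visits after treatment ends, taking day 3 as the end of treatment in both arms: days 15, 30 and 60, so 3. The count is the same whether days run from baseline (abstract) or from the end of treatment (Trial design).

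**5. Share of visits exposed, on each reading of step 1.** With 60 patients and full attendance assumed, there are 60 × 4 = 240 post-baseline visits.

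- *Per participant:* 60 × 3 = 180 visits follow disclosure, and 180 / 240 = 75%.
- *Whole trial, with disclosure once the last patient has been treated:* that last patient still has 3 visits to come, so at least 3 / 240 = 1.25% are exposed. How many more depends on how many others are still within 60 days of treatment. No accrual schedule is given, so the share cannot be fixed. It reaches 75% only if all patients finish treatment together.

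**6. Decisions after that point.** On either reading, follow-up is incomplete at disclosure. Per-protocol membership, covariate adjustment and normality handling can be settled only on complete data, so under the stated rule they may be settled by people who know the arms.

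**The case against.** The strongest reply is that post-treatment is loose drafting. For a statistician, who analyses the trial and not single patients, it could naturally mean after treatment is over for everyone, or even after the study. Day 3 is explicit for one arm only, and three of four visits is then a ceiling. This stands in part: the 75% is conditional and should not be read as a result. It does not remove the point, because the whole-trial reading still puts disclosure before the last patients' follow-up and before the analysis. The end-of-study reading is not what the text says.

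A second reply is that little is left to discretion. The primary model is fixed, the SF-MPQ is reported by patients who know their treatment, and masking the analyst does not change their answers. This also stands, and it limits the consequence. What remains open is per-protocol membership, conditional adjustment and the treatment of non-normal data. A separate analysis plan may settle the rules for these, but it would not alter the stated end of masking.

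A reader might go further and infer that outcome assessors are unmasked, because they are not on the masked list. The documents do not support that. A condensed article commonly leaves such detail to the full protocol, data handlers is undefined, and the data collection managers are described as "full-time staff who are clinically trained but not involved in the clinical intervention process". That does not prove masking, but silence does not prove its absence.

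A reader might also infer biased thermography from the sentence "The attending physician adjusts the camera focus to ensure the capture of clear thermal images". Nothing says that this physician treats patients or knows the arm, and tuina is assigned to certified therapists.

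**Conclusion.** The point holds as a badly fixed rule, not as a missing detail: the article states an end to masking, and that end can fall before follow-up and the analysis decisions are complete. It should be corrected.

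Its size depends on how disclosure would work. Up to three of the four post-baseline visits follow it if disclosure is per participant; the share is smaller and unknown if disclosure waits for the whole trial. Both figures take day 3 as the end of treatment in each arm, which is stated for the intervention arm only. The amount of bias cannot be computed from the document. For the self-reported SF-MPQ it is probably limited, because those patients are unblinded whatever the analysts know.

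The conclusion does not extend to assessor masking, to who operates the thermography camera, or to moving measurement tasks between staff.

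**What to change.** In Randomization and blinding, replace the words setting the end of masking with: until the last day-60 visit is complete, per-protocol membership is fixed and the database is locked. Add that the primary analysis will be run on coded arms (A/B), with the code broken only afterwards.

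The cost is a change of wording and a coded group variable. Someone outside the analysis must hold the key; the protocol already places envelope opening with researchers who take no part in treatment, assessment or analysis. Sample size, visits and treatment are unaffected.
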